## Abstract

The SI! Program is a long-term, school-based intervention promoting cardiovascular health across multiple age groups. This article presents the design of a new cluster-randomized controlled trial incorporating a reintervention to strengthen sustainability and promoting a school-family approach. A total of 977 children (age 6.2 years, 51.6% girls) from 50 schools in Spain were recruited. Schools were randomized to a reintervention group (intervention in second grade and reintervention in fifth grade) or a single-intervention group (intervention only in fifth grade). The primary endpoint is the change in the SI!-Child score—diet, physical activity, sleep health, and body mass index—between baseline and 5-year follow-up. The secondary endpoints include 5-year changes in SI!-Child subcomponents, sedentarism, adiposity, and the Life’s Essential 8 score and subcomponents. This revised SI! Program builds on insights from earlier trials, emphasizing adherence and long-term behavior change through a reintervention combined with active engagement of the school community and families. (The SI! Program Reintervention for Elementary Schools Trial [PSIR]; NCT06715358)

The SI! Program (*Salud Integral*–Comprehensive Health) is a multilevel, school-based intervention designed to promote cardiovascular health (CVH) in children and adolescents. Over the past 15 years, the program has been implemented and evaluated across multiple countries and educational stages, with studies assessing different exposures and intervention intensities on a range of CVH parameters.^1^, ^2^, ^3^, ^4^, ^5^, ^6^, ^7^

Evidence from these studies indicates that the retention of knowledge and habits acquired in preschool largely depends on the child’s immediate environment, as children lack the autonomy to make independent lifestyle decisions.^8^ A family-based approach is a critical complement to school-based interventions, as parents largely determine children’s access to food and opportunities for physical activity (PA) during early childhood. Consistently, evidence shows that parental behaviors and early psychosocial environments are strongly associated with children’s long-term cardiometabolic risk and lifestyle patterns later in life.^7^^,^^9^^,^^10^ By early adolescence, dietary habits already require improvement, and levels of PA—especially among girls—begin to decline.^11^^,^^12^ These findings highlight the elementary school years as a particularly favorable period for intervention: children are beginning to make more autonomous choices about their health, yet remain in a stage of high developmental plasticity and are generally free from harmful behaviors such as tobacco or alcohol use.

Throughout the evolution of the SI! Program, several key factors have been identified that influence both its implementation and effectiveness.^7^ Drawing on insights from earlier trials since the program’s launch in 2009, we have now developed a revised version. This updated strategy strengthens the role of the school environment, increases family involvement, and incorporates a reintervention during the elementary school years to promote sustainable, long-term health outcomes.

This trial also introduces the SI!-Child score, a simplified tool adapted from the American Heart Association’s Life’s Essential 8 (LE-8) score.^13^^,^^14^ Focused exclusively on behavioral components, the SI!-Child score offers a practical means of assessing CVH in young populations. The primary aim of the SI! Program Reintervention trial is to assess whether an early exposure to the SI! Program in second grade followed by a reintervention in fifth grade leads to greater improvements in the SI!-Child score than a single intervention delivered only in fifth grade among children aged 7 to 12 years.

## Methods

### Study design, population, and randomization process

The SI! Program Reintervention for Elementary Schools is a cluster-randomized trial, with schools serving as the units of randomization. In Spain, elementary education spans 6 grades and typically includes children aged 6 to 11 years. Eligible schools included public schools and charter schools initially limited to the Central, South, and East administrative areas defined by the Department of Education of the regional government of Madrid (Community of Madrid), as well as the city of Mataró (Barcelona province, Catalonia). To be eligible, schools also had to include at least one first grade class and have an operational canteen.

All schools meeting the inclusion criteria in the study areas were invited to attend informational meetings. Participation was voluntary at the school level and largely determined by institutional decisions and logistical constraints. Of the 1,026 schools in Madrid and 32 in Mataró that were invited, 50 agreed to participate. One additional school from the West administrative area of Madrid, geographically close to the boundary with the Central area, volunteered to participate and was included because it met all prespecified inclusion criteria. One school subsequently withdrew, resulting in 50 schools included in the study. Participating schools were part of the regular school systems in the study areas and represented diverse socioeconomic contexts, including public and publicly funded private schools. To reach the required sample size (see Sample Size Calculation), recruitment was conducted over 2 consecutive academic years, resulting in 2 enrollment phases: phase I (2023-2024) and phase II (2024-2025). In all, 36 schools from phase I and 15 from phase II agreed to participate (44 from Madrid and 7 from Mataró). Using block randomization stratified by school type (public vs charter), schools were assigned in a 1:1 ratio to either the reintervention group or the single-intervention group. Schools in the reintervention group were allocated to receive the SI! Program from second to sixth grade, with classroom interventions in both second and fifth grades, whereas those in the single-intervention group were allocated to receive the intervention from fifth to sixth grade, with a single classroom intervention in fifth grade (Figure 1). Schools were randomized consecutively in blocks of 6 by an independent researcher, and group allocations were communicated by email.

**Figure 1 fig1:**
[figure not shown]
**Study Design of the SI! Program Reintervention Trial** The trial includes 2 intervention groups within the SI! Program Reintervention for Elementary Schools: a reintervention group (with interventions in second and fifth grade) and the single-intervention group (intervention in fifth grade only). In addition to classroom activities, the program incorporates a reinforcement of key messages throughout the school-family environment. Teacher training takes place before intervention delivery. Red squares indicate full assessments; pink circles indicate short surveys E = environment reinforcement (school and home); I = intervention; R = reintervention; TT = teacher training and implementation planification; 0 = no intervention.

All children in first grade and their families were invited to participate. Enrollment was conditional upon signed informed consent from a parent or legal guardian. Consent forms were distributed via flyers in all first grade classrooms, including a QR code linking to an electronic version of the form, and/or as paper copies collected by teachers on behalf of the research team. In total, 977 children (mean age, 6.2 years; 51.6% girls) from 50 schools were recruited, and 963 were finally enrolled and assessed at baseline. The study flowchart, detailing school and participant recruitment and enrollment, is shown in Figure 2. Participating parents/guardians, children, and school boards have the right to withdraw from the study at any time.

**Figure 2 fig2:**
[figure not shown]
**Study Flowchart of the SI! Program Reintervention Trial** Recruitment was conducted in 2 phases: 36 schools were enrolled in phase I, and 15 in phase II. One school dropped out before baseline assessments, resulting in a total of 50 participating schools. Of these, 26 were randomized to the reintervention group and 24 to the single-intervention group. A total of 977 children provided consent to participate—588 in the reintervention group and 389 in the single-intervention group.

The trial was approved by the Regional Ethics Committee for Research with Medicinal Products (CEIm) of the Community of Madrid (CEIm-R 06/24). All collected data are managed in accordance with Spanish Law 15/1999 on the Protection of Personal Data, ensuring participant confidentiality. The study is registered at ClinicalTrials.gov (NCT06715358). This article reports the study protocol. Although baseline data collection has been completed, no baseline results are presented in this article. Protocol reporting follows the SPIRIT (Standard Protocol Items: Recommendations for Interventional Trials) guidelines,^15^^,^^16^ including the updated checklist (Supplemental Table 1) and the WHO (World Health Organization) Trial Registration Data Set (Supplemental Table 2).

### Intervention

Scientific evidence on health protective factors indicates that effective interventions extend beyond classroom-based activities to engage the entire school as an organizational unit.^17^ These interventions operate at multiple levels, including the broader school community and families.^18^^,^^19^ The underlying attitudes and values embodied by a school—and reflected in the school environment—play a fundamental role in fostering positive, healthy development among students.^20^, ^21^, ^22^ The SI! Program is grounded in the ASE model (Attitude, Social influence, and Efficacy),^23^ which draws on Social Learning Theory (also known as Social Cognitive Theory)^24^ and the Theory of Reasoned Action.^25^

The revised SI! Program retains the original components—diet, PA, body and heart awareness, and emotional management—while introducing a strengthened strategy focused on children’s environments. This enhanced approach aims to foster a sustained culture of health at both school and home and includes a new classroom intervention centered on socioemotional learning (SEL). The curriculum and accompanying educational materials were developed by the SHE Foundation (Science, Health, and Education) using innovative, participatory teaching methods.

The strategy was pilot-tested in 2023 across 4 schools in Madrid, and select resources—such as posters and family activities—were tested in 163 additional schools from the SI! Program cohort across Spain. Teachers implementing the program in their classrooms completed surveys and took part in focus groups to provide feedback on the intervention materials and activities. The findings from this pilot phase informed adaptations to both the curriculum and the evaluation tools prior to the launch of the randomized controlled trial.

### Classroom intervention

The classroom component of the SI! Program consists of teacher-led lessons focused on SEL. These sessions are designed to help children adopt and sustain healthy habits by promoting emotional awareness, self-regulation, self-esteem, and positive social relations. During the intervention period, all teachers have access to the full set of instructional materials, supporting resources, and implementation guidelines via the SI! Program website.

The classroom intervention is scheduled for delivery twice in the reintervention group (second and fifth grade) and once in the single-intervention group (fifth grade only). Each year of implementation consists of 20 hours of instruction divided across 16 sessions, with content tailored to the developmental stages of the target age groups (7-8 years in second grade, and 10-11 years in fifth grade).

### School and family environment

The enhanced strategy for the school environment in the revised SI! Program is designed to encourage self-assessment by the school community and to support the development of feasible plans for improvement. A key tool in this process is the *Healthmeter* (*Saludómetro*), a structured tool that helps schools assess the presence and quality of health-promoting routines and resources (Supplemental Figure 2). The environmental intervention is led by a dedicated *Leading group* composed of school staff, students, and family members committed to health promotion. This group conducts the *Healthmeter* assessment and uses supporting guides—with practical and theoretical examples—to identify and implement appropriate changes. The *Leading group* is also responsible for ensuring the overall implementation of SI! Program activities at the school level.

The strategy also includes an annual school-wide event, *Healthy Day*, which is organized by the school community around a rotating theme drawn from the SI! Program’s core components. The current iteration introduces a new emphasis on rest, broadly defined to include not only sleep routines but also breaks and recovery periods. Activities are tailored to different age groups, and the event is designed to reinforce a shared culture of health across all school levels and among families.

In addition, families receive several newsletters during the academic year. These include instructions for using the *Healthmeter*, provide information about the *Healthy Day* theme, and include other educational resources and guidance to support healthy habits at home.

### Teacher training and implementation monitoring

Formal training is provided annually by the SHE Foundation: 30 hours for the classroom intervention and 20 hours for the school environment component, specifically for members of the *Leading group*. Implementation is monitored through periodic reports submitted by teachers and the *Leading group*, documenting the progress of SI! Program activities at both the classroom and school-environment levels. In addition, the SHE Foundation coordination team issues periodic communications with reminders of key intervention milestones each year, including teacher training activities. Ongoing support is also provided by email and telephone, with the possibility of individual meetings to assist teachers and Leading Groups with any aspect of program implementation. These monitoring procedures will inform the assessment of implementation fidelity, dose, reach, and participant satisfaction, which will be integrated into a composite implementation index.

Additional details on the intervention are provided in the Supplemental Methods.

### Data collection

The schedule of enrollment, interventions, and assessments for the SI! Program Reintervention trial is summarized in Figure 3. Full participant assessments are scheduled at baseline and at 3- and 5-year follow-up. These include the complete set of LE-8 components, with detailed evaluation both of health behaviors (diet, PA, nicotine exposure, and sleep health) and of health factors (body mass index [BMI], lipid profile, blood glucose, and blood pressure [BP]), as well as body composition indicators such as waist circumference (WC) and body fat mass.

**Figure 3 fig3:**
[figure not shown]
**Study Timeline of the SI! Program Reintervention Trial** Timeline of enrollment, intervention delivery, and assessment activities for schools enrolled in phase I and phase II of the SI! Program Reintervention trial. The figure shows the planned time points for classroom intervention, environment reinforcement (school and home), full health assessments, short survey, and implementation checklists, spanning academic years 2023 to 2031.

Measurements will be conducted during school hours by a team of trained nutritionists and nurses. Parents/caregivers will complete questionnaires about their child’s and their own lifestyle behaviors through a dedicated data management application, due to the limited ability of young children to accurately report these behaviors. For families without email access, printed copies will be provided.

After each assessment, families will receive a brief medical report summarizing results and including recommendations for follow-up with their primary care physician, if needed. In addition to the main assessments, families will complete short questionnaires at 1-, 2-, 4-, and 6-year follow-up (Figure 1), covering child diet, PA, nicotine exposure, sleep health, and parent/caregiver-reported weight and height. Every effort will be made to follow-up all participants, including those who change schools.

### Diet

Children’s diets will be reported by families using an adapted version of the validated Children's Eating Habits Questionnaire–Food Frequency Questionnaire.^26^, ^27^, ^28^

### Physical activity and sleep

Participants will wear an Actigraph wGT3XBT accelerometer on the nondominant wrist for 7 consecutive days to assess the amount and intensity of PA and sleep patterns.^6^^,^^29^^,^^30^ Families will also report children’s PA using a dedicated questionnaire derived from the validated QAPACE (Quantification de L’Activité Physique en Altitude chez les Enfants) survey.^31^ Additional questions will capture sleep-related habits—including bedtimes and wake-up times on weekdays and weekends and the frequency and duration of naps—and screen time (both leisure and nonleisure) on weekdays and weekends.

### Nicotine exposure

Nicotine exposure will be assessed based on reported use of combustible tobacco or electronic nicotine delivery systems (e-cigarettes or vapes) among participants aged 12 years and older, and/or reported smoking within the immediate household or environment for younger participants.

### Anthropometry and body composition

Body weight will be measured using an OMRON BF511 body composition scale, and height with a Seca 213 portable stadiometer, with participants wearing light clothing and no shoes. Weight and height will be recorded to the nearest 0.1 kg and 0.1 cm, respectively. BMI will be calculated as weight divided by height squared (kg/m^2^).

WC will be measured in triplicate using a Holtain metric tape (accuracy ±0.1 cm), following gentle expiration. The tape will be positioned in a horizontal plane around the abdomen, between the lowest rib and the top of the right iliac crest.

Total body fat will be estimated by bioelectrical impedance analysis with a tetrapolar OMRON BF511 device.

### Glucose and lipid profile

Capillary blood samples will be collected via lancet to measure blood glucose, total cholesterol, high-density lipoprotein cholesterol, low-density lipoprotein cholesterol, non–high-density lipoprotein cholesterol, and triglycerides. Analyses will be performed with a CardioCheck Plus device and PTS Panel test strips.^32^

### Blood pressure

BP will be measured twice at 2 to 3 minutes intervals using an OMRON M6 monitor. If the difference between the 2 systolic readings exceeds 10 mm Hg or the difference between the 2 diastolic readings exceeds 5 mm Hg, a third measurement will be taken. For analysis, the pair of readings with the lowest systolic BP will be selected; in the case of a tie, the pair with the lowest diastolic BP will be used.

### Family

The family questionnaire will collect information on a range of sociodemographic variables, including parental or caregiver country of birth, household income, family structure, parental or caregiver education level, occupation, and social support network. Household income will refer to total net annual income, categorized into quintiles using the most recent regional data from the Spanish National Statistics Institute at baseline.^33^ Family structure will be defined by the adult relatives or caregivers living in the household (eg, biological or adoptive parents, grandparents).^34^ The highest household educational level will be reported, according to the International Standard Classification of Education,^35^ and occupation will be reported according to the European Socioeconomic Classification.^36^ Social support will be assessed with the question “How many persons, other than your family, do you know that you can definitely rely on in cases of need?”^37^

In addition, data will be collected on parental or caregiver lifestyle behaviors, including diet, PA, smoking habits, and self-reported BMI and BP.

### Definition of health scores

#### SI!-Child score

The SI!-Child score is a simplified tool adapted from the LE-8 scale to assess and monitor lifestyle-related metrics for CVH screening in children and adolescents. This score was designed to capture behavior change and facilitate repeated monitoring in educational school-based interventions. Details of its development and assessments of agreement with the lifestyle-related LE-8 components are provided in the Supplemental Methods and Results. The SI!-Child score incorporates 5 behavioral metrics derived from the LE-8 score: diet, PA, nicotine exposure, sleep health, and BMI. Each metric is scored on a 0 to 100 scale. The overall SI!-Child score is calculated as the unweighted average of the 5 components and categorized as poor (0-49 points), intermediate (50-79 points), or ideal (80-100 points)^13^ (Figure 4). In this trial, nicotine exposure will not be included in the calculation of the SI!-Child score, given the negligible prevalence of active smoking in young children and because nicotine exposure is primarily determined by environmental factors rather than direct child behavior. Therefore, the SI!-Child score will be derived as the unweighted average of the 4 remaining components and categorized according to the established thresholds.

**Figure 4 fig4:**
[figure not shown]
**Components and Scoring Structure of the SI!-Child Score** Each of the 5 individual components of the SI!-Child score is rated on a scale from 0 to 100 points. The overall score is calculated as the unweighted average of the 5 component scores and ranges from 0 to 100. Scores are categorized as follows: poor (0-49), intermediate (50-79), or ideal (80-100). s/day = servings per day; s/week = servings per week.

The diet metric is a composite of 5 food groups derived from the food frequency questionnaire: fruits and vegetables, legumes and nuts, fast food, sugared beverages, and sweets and pastries. Each food group is assigned a score from 0 to 20 points.

The PA metric will be assessed primarily through accelerometer-measured weekly minutes of moderate-to-vigorous PA, supplemented by questionnaire responses. A score of 100 is assigned for ≥420 minutes of moderate-to-vigorous PA per week.

Sleep health will be assessed as the average number of hours slept per 24-hour period, using accelerometer data supported by questionnaire information. The ideal range for children aged 6 to 12 years is 9 to 12 hours per day.

BMI categories will be categorized according to age- and sex-adjusted reference percentiles. Normal weight, defined as a BMI between the fifth and 85th percentile, is considered ideal.

#### Life’s Essential 8 score

The LE-8 score of CVH for children and adolescents includes 8 metrics: diet, PA, nicotine exposure, sleep health, BMI, blood lipids, blood glucose, and BP.^13^ The original scoring criteria for these components, along with the specific adaptations used in this study, are summarized in Supplemental Table 3.

#### Hypothesis and endpoints

The study hypothesizes that children exposed to the SI! Program in both second and fifth grade (reintervention group) will show greater improvement in the SI!-Child score and related health parameters over 5 years than those receiving the program only in fifth grade (single-intervention group). The primary endpoint is the between-group difference at 5-year follow-up in the overall SI!-Child score (range, 0-100), encompassing diet, PA, sleep health, and BMI. Secondary endpoints include the between-group differences in the 5-year change in the SI!-Child subcomponents, the LE-8 score and its individual components (diet, PA, nicotine exposure, sleep health, BMI, blood lipids, blood glucose, and BP), as well as measures of sedentary behavior and adiposity markers.

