### Statistical methods

#### Sample size calculation

Sample size estimates were based on a cluster-randomized design and calculated using the *clustersampsi* command (Stata version 15.0). Drawing on pilot data (mean SI!-Child score excluding nicotine exposure at ages 7-8 = 70.62; SD = 11.77), a minimum of 40 schools (20 per study arm) was required to detect a 5% difference in SI!-Child score (excluding nicotine exposure) between groups, with 80% power and a 2-sided significance level of 0.05.

Additional parameters included an average of 20 children per school, a coefficient of variation of cluster (school) sizes of 0.51, and an intraclass correlation coefficient of 0.05. To account for potential loss to follow-up, the target sample was increased to 42 schools (21 per arm), corresponding to an expected enrollment of 840 children.

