#### Statistical analysis plan

The descriptive analysis will summarize baseline data, including demographic variables (eg, gender, age, place of birth), socioeconomic indicators (eg, household income, parental or caregiver education level and country of birth), and study-specific variables (eg, SI!-Child scores; lifestyle habits such as diet, sleep, and PA; adiposity measures; and blood parameters). Continuous variables will be presented as means and SDs, and categorical variables as frequencies and percentages.

Primary endpoint differences will be evaluated using all available measurements at baseline and at 5-year follow-up. The intervention effect will be estimated using multilevel mixed-effects models for repeated measures. The model will include fixed effects for time of assessment (baseline vs follow-up), randomization group (reintervention vs single-intervention), and the interaction between time and randomization group. The treatment effect will be estimated from the time-by-randomization interaction term, representing the between-group difference in change in SI!-Child score over time. Random intercepts for school and participant will be included to account for clustering at the school level and repeated measurements within individuals. Similar multilevel mixed-effects logistic regression models will be applied for categorical outcomes, and the same analytical strategy will be used to evaluate secondary endpoints.

The primary analysis will follow the intention-to-treat principle, including all randomized enrolled participants according to their allocated group. Models will be estimated using maximum likelihood, which provides valid inference under a missing-at-random assumption and uses all available data without requiring imputation. Models may additionally adjust for prespecified baseline covariates (eg, baseline outcome value, age, gender, and stratification variable) to improve precision.

Sensitivity analyses will be conducted to evaluate the robustness of the findings to alternative assumptions about missing data. These will include 1) complete-case analyses restricted to participants with both baseline and follow-up outcome measurements; 2) multiple imputation procedures; 3) additional sensitivity analyses exploring potential missing-not-at-random mechanisms, and other statistical approaches such as cluster-level analyses or Analysis of Covariance models of follow-up outcomes adjusted for baseline values.

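### The primary endpoint is worded as a 5-year level in one place and a 5-year change in others, and the stated 80% power belongs to an unadjusted single-time-point comparison, not the planned test of change

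*Protocol article*

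**What the plan says.** Four places in the protocol article bear on the point.

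- **Abstract:** "The primary endpoint is the change in the SI!-Child score", measured between baseline and 5-year follow-up.
- **Hypothesis and endpoints:** "The primary endpoint is the between-group difference at 5-year follow-up in the overall SI!-Child score (range, 0-100". The next sentence words the secondary endpoints differently: "Secondary endpoints include the between-group differences in the 5-year change in the SI!-Child subcomponents".
- **Statistical analysis plan:** "The treatment effect will be estimated from the time-by-randomization interaction term, representing the between-group difference in change in SI!-Child score over time". The random effects are given as: "Random intercepts for school and participant will be included to account for clustering at the school level and repeated measurements within individuals". No school-by-time term is named. Adjustment for the baseline outcome is something the models may do, and an analysis of covariance of follow-up values appears only among the sensitivity analyses.
- **Sample size calculation:** 40 schools (20 per arm) were "required to detect a 5% difference in SI!-Child score (excluding nicotine exposure) between groups, with 80% power", from pilot data with "mean SI!-Child score excluding nicotine exposure at ages 7-8 = 70.62; SD = 11.77". The other inputs are 20 children per school, a coefficient of variation of school size of 0.51 and an ICC of 0.05. The section gives no SD of change and no correlation over time for schools or children.

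**The concern.** Taken literally, the endpoint section makes the primary endpoint a level at five years and the secondary endpoints changes, while the Abstract and the analysis make the primary endpoint a change. Under randomization both have the same expected treatment effect. In one dataset, however, they give different estimates and standard errors whenever the arms differ at baseline, and here the arms contain 588 and 389 consented children. The definition should leave no choice between them.

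Power has a related problem. The variance of a level at one time point needs only an SD and an ICC. The variance of a difference in change also needs the persistence of school effects and of children's scores over five years. A power figure computed without those quantities does not describe the interaction test.

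**Working it through.** **Inputs from the Sample size calculation section:** mean 70.62, SD 11.77, m = 20 children per school, CV = 0.51, ICC = 0.05, two-sided alpha 0.05, power 80%.

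**1. Reproducing the stated 40 schools**

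- Target difference: 0.05 × 70.62 = 3.531 points.
- Children per arm without clustering: 2 × (1.96 + 0.8416)² × 11.77² / 3.531² = 174.4.
- Design effect: 1 + [(1 + 0.51²) × 20 − 1] × 0.05 = 2.210.
- Schools per arm: 174.4 × 2.210 / 20 = 19.3, rounded up to 20.
- With 20 schools per arm, SE = 11.77 × √(2 × 2.210 / 400) = 1.237. Power is 81.4% (normal) or 79.4% (t, 38 df).
- Reading 5% as 5 points gives 87.0 × 2.210 / 20 = 9.6, or 10 schools per arm, which does not match.

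The stated figure is therefore arithmetically sound for an unadjusted single-time-point comparison at 3.53 points.

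**2. Power for the difference in change**

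Let c be the correlation of a school's effect between baseline and five years, and i the correlation of a child's within-school deviation over the same period. Neither is in the article, so all values of c and i are assumptions. With K schools per arm, the variance per arm is:

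- Change: 11.77² × [2 × 0.05 × (1 − c) × (1 + 0.51²) + 2 × 0.95 × (1 − i) / 20] / K
- 5-year score adjusted for baseline: 11.77² × [0.05 × (1 − c²) × (1 + 0.51²) + 0.95 × (1 − i²) / 20] / K

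Example, c = 0.5, i = 0.3, K = 20: the change bracket is 0.0630 + 0.0665 = 0.1295. SE = 11.77 × √(2 × 0.1295 / 20) = 1.339, and 3.531 / 1.339 − 1.96 = 0.68, so power is 75%.

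Results (normal approximation, before losses):

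| School / child correlation | Change, 40 schools | Change, 50 schools, equal split | Baseline-adjusted, 40 schools |
|---|---|---|---|
| 0.2 / 0.2 | 62% | 71% | 83% |
| 0.5 / 0.3 | 75% | 84% | 88% |
| 0.8 / 0.4 | 91% | 96% | 97% |
| 1 / 0.2 to 0.5 (school effect constant) | 93-99% | 97% or more | 99% or more |

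The last row corresponds to the model as written, because a single random intercept per school holds the school effect fixed over time. At the opposite extreme, with school effects unrelated across five years (0 / 0.2), change has 56% and the baseline-adjusted analysis 82% at 40 schools. With both correlations at zero, the adjusted formula reduces to the level comparison, 81.4%.

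**3. A simpler cross-check**

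Keep the ICC at 0.05 for change as well, and take SD of change = 11.77 × √(2(1 − r)). Power at 40 schools is then 62% at r = 0.2, 74% at r = 0.4, 81% at r = 0.5 and 96% at r = 0.7. The stated 80% carries over to change at about r = 0.5, a condition the article does not state.

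**The case against.** The strongest reply is that the mismatch is a slip of wording. The analysis section names one primary estimator, the Abstract agrees with it, and the hypothesis sentence directly before the endpoint definition speaks of improvement over five years. Nothing in the article plans an unadjusted 5-year comparison as the primary test. This stands. A reader might infer that two rival primary analyses are open, but the article does not support that.

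A reader might also infer that the trial is underpowered. That is not supported either. The correlations are unknown, power for change lies on both sides of 80% depending on them, and under the random-intercept model as written it is above 90%. Recruitment also exceeded the target, with 50 schools against 42. Whether school effects really stay constant for five years is a separate modelling question.

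Nor is the 5% a real ambiguity. The mean stands in the same sentence, and only 5% of that mean reproduces the stated number of schools. Stating 3.53 points would simply be clearer.

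Finally, an article condenses its protocol, and fuller assumptions may exist elsewhere. That could excuse a missing correlation. It does not excuse two different definitions of the primary endpoint, or a power figure presented without saying which comparison it refers to.

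**Conclusion.** The point holds in a limited form and should be fixed. The endpoint section contradicts the Abstract and the analysis section on whether the primary endpoint is a level or a change; confidence in this is high. The 80% is correct for an unadjusted single-time-point comparison at 3.53 points, but was not derived for the interaction test.

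How far power for the planned test differs from 80% cannot be settled from the article. At 40 schools the tabulated scenarios run from 62% to 99%, and at 50 equally split schools from 71% upwards. All of these rest on assumed correlations, the pilot SD and ICC, a normal approximation and no attrition. The direction of the difference is unknown, and no shortfall is demonstrated. The consequence is an unclear definition and a mislabelled power statement.

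**What to change.** 1. **Use one definition.** Reword the primary endpoint in the Hypothesis and endpoints section to agree with the Abstract and the interaction test. This costs one phrase.
2. **Preferably, make the baseline score a fixed part of the primary analysis.** The target would be the 5-year difference adjusted for baseline, which under randomization is the same as for the difference in change. The analysis of covariance already listed as a sensitivity analysis would serve, with school clustering retained. In every scenario above it has more power than unadjusted change, about 82% or more at 40 schools before attrition. This changes the primary estimator in the Statistical analysis plan section, so it needs a documented amendment, and the Abstract and endpoint section must then follow it. The baseline data are already collected.
3. **Correct the power statement.** Either label the 80% as referring to an unadjusted single-time-point comparison at 3.53 points, or restate power for the chosen analysis. A restatement should use the 50 schools recruited and a stated range of school and child correlations that includes a constant school effect.

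None of this needs more participants, visits or measurements. The cost is some wording, one recalculation and, if step 2 is taken, one amendment. The stated power may become a range.
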